### Criteria for discontinuing or modifying allocated interventions {11b}

If a participant’s health condition deteriorates to the extent that they no longer meet the inclusion criteria, their participation in the study may be terminated by the researchers or by the OT in collaboration with the researchers.

The intervention is person-centered and tailored to each participant’s individual needs to achieve a personal and activity-based goal. It incorporates progression, in which the level of challenge in the training activities is gradually increased as the participant’s functional abilities improve. Consequently, the content and difficulty of the support plan are expected to be adjusted throughout the intervention. The criteria for these adjustments are based on the progression outlined in the goal-oriented support plan.

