### Eligibility criteria {10}

RAC facilities in the specific municipality having wards with somatic specialization are eligible for the research project. The RAC facilities should not be involved in other rehabilitation research projects at the time, and they should have a stable staffing situation.

The staff supporting the older adults in the Re-RAC intervention will include nursing assistants, registered nurses, PTs, and OTs. They must be regularly employed or, in the case of external employment, be regular consultants at the RAC facilities and have completed the Re-RAC training.

Older adults aged 65 years and above, residing in a somatic ward at a RAC facility where the study will be conducted and meeting the inclusion criteria, are eligible to participate in the study. The inclusion criteria require that the older adult must be able to engage in conversations in Swedish and be able to participate in both the assessments and the intervention. Persons having severe cognitive impairment (≤ 17) [36] according to Mini Mental State Examination—Swedish version (MMSE-SR; screening for cognitive function [37]) or being very severely frail or terminally ill according to the Clinical Frailty Scale (≥ 8) (CFS-9, Swedish version [38]) will be excluded. The psychometric features for the MMSE-SR and CFS-9 are reportedly good [36, 38].

Personnel, irrespective of profession, who have completed the Re-RAC training, have worked with the intervention with at least one participant, and are Swedish speaking are eligible to participate as staff informants in the focus-group interviews.

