## Assignment of intervention: blinding

### Who will be blinded {17a}

This study evaluates an intervention in which participants from both allocation groups may reside in the same ward, making it impossible to blind either the participant or the staff to their group assignment. Additionally, the nature of the intervention, which includes a training component delivered by the staff, precludes blinding for these groups. However, all researchers, except one, will remain blinded during the analyses. The unblinded researcher will be responsible for administering, collecting, and securely storing the coded data. This researcher will also be involved in the data collection and delivery of the intervention and therefore cannot be blinded to the randomization or the participants’ study IDs. Data entry into the electronic case report form (e-CRF) system called Greenlight Guru Clinical (GGC) will be performed by the unblinded researcher. Study ID numbers will remain concealed from the rest of the research team during the analyses. Outcome assessors and analysts, apart from the designated unblinded researcher, will remain blinded to group allocation. Statistical analyses will be conducted by an external, blinded statistician.

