### Plans to promote participant retention and complete follow-up {18b}

Upon enrollment in the study, the research team will encourage participants to adhere to the intervention and complete the follow-up. However, it must be acknowledged that participants in this research project reside in RAC facilities and are, to some extent, frail. Their health status may deteriorate during the trial, potentially impacting retention rates in both groups. To support participant retention, flexible scheduling of interviews and data collection will be offered, including the option to divide follow-up interviews into shorter sessions to reduce fatigue. In addition, regular check-ups by rehabilitation staff will be provided to both participants and nursing assistants to maintain engagement and identify early signs of withdrawal risk. The research team will also work in close collaboration with RAC staff to facilitate reminders and logistical support. Clear and respectful communication will be emphasized throughout, highlighting the importance of each participant’s contribution to the study.

In the event that a participant discontinues the intervention or withdraws from the study, the research team will request permission to collect available follow-up data, if ethically and practically feasible. When provided, the reason for withdrawal will be documented. All data collected up to the point of withdrawal will be included in the final analysis, in accordance with the intention-to-treat principle.

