### Health-economic analysis

A cost–utility analysis using individual data will be performed from a healthcare perspective [58]. Cost-effectiveness ratios will be based on the changes in QALY and net costs for the intervention group compared with the control group. Results will be presented as an incremental cost-effectiveness ratio (ICER), expressed as ICER = Ca − Cb/Ea − Eb, where Ca and Cb represent the costs for the intervention and control groups, respectively, and Ea and Eb represent the QALY changes for the intervention and control groups, respectively. Sensitivity analyses will be conducted to account for uncertainty in parameter estimates by incorporating both British [59] and Swedish [60] value sets for the health state preferences, as well as varying costing approaches.

QALYs will be derived from the EQ-5D-5L [44–46] using the summary index score based on societal preference weights (“utilities”). The health state index scores range from less than 0 (a health state equivalent to dead, with negative values representing values worse than dead) to 1 (the value of full health). Health state preferences typically represent national or regional values and can therefore vary among countries or regions. In this study, both the widely used British value set [59] and the recently developed Swedish value set [60] will be applied.

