### Methods in analysis to handle protocol non-adherence and any statistical methods to handle missing data {20c}

Protocol non-adherence will be managed according to the ITT principle, analyzing all randomized participants according to their original randomization assignment, regardless of withdrawal, protocol deviations, or noncompliance. Missing values within each instrument will be handled according to the instructions provided in the respective instrument manuals, if available. Other missing data will be addressed using multiple imputation by chained equations.

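### The rule that lets the team end study participation on deterioration {11b} is not reconciled with {18b} and {20c}, and can create avoidable missing data related to the outcome

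*Protocol article*

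**What the plan says.** All references are to the protocol article.

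- **{11b}, discontinuing or modifying interventions.** The heading concerns the allocated intervention, but the consequence named is the end of study participation. If deterioration means the inclusion criteria are no longer met, "their participation in the study may be terminated by the researchers or by the OT in collaboration with the researchers".
- **{10}, eligibility.** The inclusion criteria are ability to converse in Swedish and to "be able to participate in both the assessments and the intervention". The cognitive and frailty cut-offs are worded as exclusions, and Table 1 schedules those two instruments only at enrolment.
- **{17a}, blinding.** Both arms may live on one ward, "making it impossible to blind either the participant or the staff to their group assignment". On the research side: "However, all researchers, except one, will remain blinded during the analyses". The exception is the researcher who takes part in data collection and in delivering the intervention.
- **{18b}, retention.** If a participant discontinues or withdraws, the team will ask to collect what follow-up data it can, within ethical and practical limits. "All data collected up to the point of withdrawal will be included in the final analysis".
- **{20c}, non-adherence and missing data.** The intention-to-treat analysis means "analyzing all randomized participants according to their original randomization assignment, regardless of withdrawal, protocol deviations, or noncompliance". Apart from the scoring rules in instrument manuals, "Other missing data will be addressed using multiple imputation by chained equations".
- **Table 1.** COPM, EQ-5D-5L, WHO-5 and accelerometry are taken at week 0 and week 9 only. Records are extracted for weeks −12 to 0 and 9 to 20.

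**The concern.** Decline in health after randomisation is closely tied to what COPM-P, EQ-5D-5L and WHO-5 measure. A rule that lets the team end study participation because of decline therefore produces missing outcomes that depend on the outcome. Standard multiple imputation assumes data missing at random given what was observed, and does not repair this kind of loss.

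The rule can also act unevenly. One inclusion criterion is ability to take part in the intervention, and during the eight weeks only the Re-RAC arm puts that ability to the test. The occupational therapist (OT) who shares in the decision supervises Re-RAC, and the week 3 and week 6 check-ups are described as Re-RAC support (preparatory training section and {11c}). Under {11d}, control participants receive no active help with their goal, and the OT is informed only once the trial period is over. If removals, or the prognosis of those removed, differ by arm, the treatment comparison is biased.

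**Working it through.** **1. The sections side by side.** {20c} keeps every randomised participant in the analysis whatever happens later. {18b} provides for follow-up when the participant discontinues or withdraws. {11b} adds a third route, termination by the team, and neither {18b} nor {11b} says whether follow-up is still sought on that route. With one outcome visit after baseline, at week 9, someone terminated earlier and not followed up has baseline values only for COPM-P and the other assessed outcomes. The sentence in {18b} on data collected before withdrawal then adds no follow-up outcome. {11b} does not say whether record extraction for weeks 9 to 20 continues.

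**2. The plan's own numbers.** Inputs from {14}: difference 0.9, SD of change 1.3, two-sided α 0.05, power 80%, dropout 25%, 43 per arm.
- A two-sample t-test needs 34 per arm, and 34 × 1.25 = 42.5, rounded up to 43 per arm or 86 in total. The stated figure is reproduced.
- Planned loss: 0.25 × 43 = 10.75 per arm, or 21.5 of 86. This is dropout from all causes; the article does not say how much is termination under {11b}.

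**3. Formula for the bias.** Let p be the share of an arm with an imputed outcome, and d the amount by which those people truly fall below their imputed values. Imputation overstates that arm's mean by p × d. The between-arm difference is therefore misstated by

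bias = p(Re-RAC) × d(Re-RAC) − p(TAU) × d(TAU).

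A positive value favours Re-RAC.

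**4. Results.** The splits and shortfalls are assumptions; the article gives neither.

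| Missing, Re-RAC vs TAU | Shortfall d | Bias (COPM-P units) | Share of 0.9 |
|---|---|---|---|
| 25% vs 25% | equal in both arms | 0 | 0% |
| 15% vs 10% | 2 | 0.30 − 0.20 = 0.10 | 11% |
| 30% vs 20% | 1 | 0.30 − 0.20 = 0.10 | 11% |
| 30% vs 20% | 2 | 0.60 − 0.40 = 0.20 | 22% |
| 20% vs 30% | 1 to 2 | −0.10 to −0.20 | 11% to 22%, against Re-RAC |
| 25% vs 25% | 1.3 vs 0.5 | 0.25 × 0.8 = 0.20 | 22% |

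The 30% versus 20% split keeps the planned total: 12.9 + 8.6 = 21.5 people. The last row shows that equal removal rates are not enough if those removed differ in prognosis by arm.

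**The case against.** The strongest reply is that {18b} already plans follow-up after discontinuation or withdrawal, with a sensible limit on what is ethical and feasible, and that {20c} keeps everyone in the assigned arm. On that view only a cross-reference is missing. Much of this stands: the follow-up intention exists, and what is open is whether it reaches terminations started by the team. But an analysis plan cannot recover week 9 data that were never sought, so the gap has to be closed in the conduct rules.

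Uneven detection is plausible, not shown. OTs are stationed at every facility, participants in both arms may continue existing rehabilitation {11d}, and {18b} mentions check-ups for participants in general terms. The size also rests on assumed inputs, and the shortfall must be measured from the imputed values. If the imputation model explains part of the decline through baseline covariates, d is smaller than the gap from completers.

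Three stronger readings are tempting, and the article does not support them:
- *The rule defeats intention-to-treat.* It does not. All randomised participants are analysed as allocated; the problem is missing data.
- *Unblinded staff decide alone.* The OT acts only together with the researchers, and the researchers who may decide are not limited to the unblinded one.
- *Removed participants, including any who die, are imputed as if they were completers.* {20c} names the method but not the model. The handling of deaths, utility after death and sensitivity analyses may be set out in the statistical analysis plan {5d} or in the health-economic analysis plan cited under health-economic parameters. Neither is shown, so silence here is no error.

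**Conclusion.** The point holds as a conflict in the conduct rules. {11b} allows study participation to end at discretion, on grounds related to the outcome and with input from staff who know the allocation, while {18b} and {20c} aim at complete follow-up of everyone randomised. The missing data this creates are avoidable. The bias is zero if removal and prognosis are balanced, and its direction depends on which arm loses more. Under the assumed 30% versus 20% removal and a shortfall of 1 to 2 units from the imputed values, it is 0.10 to 0.20 COPM-P units, 11% to 22% of the target difference. It would be smaller if only part of the 25% dropout arises under {11b}. The matter is worth correcting, but it does not invalidate the intention-to-treat analysis.

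**What to change.** Reconcile {11b}, {18b} and {20c} by stating that no longer meeting the inclusion criteria after randomisation does not by itself end follow-up in either arm. Specifically:

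- The week 9 assessment is still attempted where the participant is willing and able. The ethical and practical limit in {18b} applies, including where capacity is lost, since {26a} makes no provision for authorised representatives.
- Record extraction continues unless consent is withdrawn.
- {18b} says explicitly that it covers terminations decided by the team.
- Any decision about the intervention itself is left as the protocol has it.

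The cost is a wording change. The week 9 visits and record extraction are already planned, and the trial status section expects recruitment and data collection to run to the end of 2026, so the change can still prevent loss. The downside is that some week 9 interviews will be incomplete. Separately, and not part of this finding, the handling of deaths in the imputation and in the QALYs should be confirmed in the statistical and health-economic analysis plans.

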### Strategies to improve adherence to interventions {11c}

The goals of the intervention are person-centered, and the content of the intervention, including the activities designed to achieve the participant’s goal, is planned in collaboration with the participant. This collaborative approach is expected to enhance the participant’s motivation for and adherence to the intervention. Additionally, meetings with the OT after 3 and 6 weeks provide opportunities to discuss and adjust the support plan as needed, further supporting adherence. An information sheet will also be provided to participants, intended to be shared with relatives, to inform them about the study and potentially facilitate additional support from them. The support plan and the goal will also be visualized in each participant’s apartment.

To enhance the nursing assistants’ motivation and engagement, they will have access to support and supervision from the OT throughout the intervention period, as needed. Check-ups with the OT will be offered to both the older adult and the nursing assistants during weeks 3 and 6. The check-ups are intended to identify any need for changes in the goal-oriented support plan and to provide ongoing support for both the participant and the nursing assistants in progressing through the Re-RAC intervention. Additionally, the check-ups with the nursing assistants are also designed to help them maintain the participants’ motivation and engagement, thereby promoting adherence to the intervention.

To assess adherence to the intervention, all staff at the RAC facility are required to complete a logbook, as described later in this protocol. Adherence can also be partially monitored through the Medication and Care Support System (MCSS).

### Relevant concomitant care permitted or prohibited during the trial {11d}

RAC facilities included in the study must not concurrently participate in other rehabilitation-related research during the trial period. Re-RAC will be evaluated against TAU, which includes access to standard rehabilitation services when clinically indicated. Accordingly, participants in both the intervention and control groups may continue receiving ongoing rehabilitation programs—such as physiotherapy or occupational therapy—intended to maintain functional ability. These services will not be withdrawn or modified for control group participants and will proceed as per the conditions at the time of study inclusion. Adjustments will only be made if a new rehabilitation need arises that cannot be postponed.

Control group participants will set a goal but will not receive active support to achieve it during the trial period. Once this period concludes (after three months), the facility’s responsible occupational therapist will be informed, and the participant may then be offered Re-RAC outside the study framework.

For participants in the Re-RAC group, any existing rehabilitation services will be supplemented with actions outlined in the Re-RAC plan. Services in place at the time of inclusion may be modified if such adjustments better support the participant’s goal attainment during the intervention phase.

### Provisions for post-trial care {30}

No provisions for post-trial care are planned, given the expected low risk of harm associated with participation in the trial. Upon completion of the study, participants will continue with TAU based on medical indications and current guidelines. All participants are covered by patient insurance.

### Outcomes {12}

#### Primary outcome

The primary outcome is the mean change in occupational performance related to the prioritized activity, measured with COPM-P [42, 43], immediately after the 8-week intervention period. The comparison will be made between participants who have undergone the Re-RAC intervention and those receiving TAU.

#### Secondary outcomes

Secondary outcomes will compare mean changes from baseline to, 8 weeks from baseline, between older adults who have undergone the Re-RAC intervention and those receiving TAU in the following areas:Self-perceived satisfaction with occupational performance in the prioritized activity, measured using the COPM-S [42, 43];Self-perceived health-related quality of life, assessed with the EQ-5D-5L [44–46];Self-perceived psychological wellbeing, measured with the WHO Well-Being Index (WHO-5) [47]; and.Level of physical activity, assessed using an accelerometer (advanced pedometer) worn for seven consecutive days both before and immediately after the intervention; physical activity data will be supplemented with a diary documenting accelerometer wear time.

To explore any possible associations between pain and other outcomes, pain will be assessed using the pain dimension of the EQ-5D-5L.

Older adults’ experiences of the intervention will be investigated through individual semi-structured interviews conducted after completion of the intervention.

The experiences of staff involved in delivering the intervention will be investigated through focus-group interviews.

Finally, cost-effectiveness will be evaluated from a healthcare perspective by calculating the costs per quality-adjusted life year (QALY) gained.

### Participant timeline {13}

Table 1 and Fig. 1 summarize the schedule of enrollment, intervention, and data collection.

**Table 1 Tab1:** Schedule of enrollment, interventions, and assessments

	**Study period**					
	**Enrollment**	**Baseline**		**Intervention**	**Post-intervention**	
**TIMEPOINT**	**w – 1 **	**w – 12 to w0**	**w0**	**w1 to w8**	**w9**	**w9 to w20**
**ENROLLMENT:**						
**Informed consent **	X					
**Eligibility screen**	X					
*MMSE-SR*	X					
*CFS-9*	X					
**Allocation**	X					
**INTERVENTIONS:**						
Intervention group				Re-RAC + TAU		
Control group				TAU		
**DATA COLLECTION:**						
*COPM*			X		X	
*EQ5D-5L*			X		X	
*WHO-5*			X		X	
*Accelerometers*			X		X	
*Interview participants*					X^a^	
*FGD nursing assistants*					X^b^	
*Medical records and administrative systems*		X				X

*CFS* Clinical Frailty Scale, *COPM* Canadian Occupational Performance Measure, *W* week, *FGD* focus group discussion, *MMSE-SR* Mini Mental State Examination—Swedish version, *TAU* treatment as usual, *Re-RAC* Reablement in Residential Aged Care

### Sample size {14}

A total of 86 individuals (*n* = 43 per group) will be included to detect an improvement of 0.9 units in the primary outcome, i.e., occupational performance, as measured using the Canadian Occupational Performance Measure—performance (COPM-P), between the intervention and control groups. This calculation assumes 80% power, a significance level of *α* = 0.05, and a two-sided *t*-test, with a standard deviation of 1.3 units for the change in COPM-P, and a 25% dropout rate. This corresponds to a moderate effect size (Cohen’s *d* = 0.5, with a baseline standard deviation of 1.8). Assumptions regarding the standard deviation, treatment effect, and dropout rate are based on findings from our previous feasibility study [28].

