**Fig. 1 Fig1:**
[figure not shown]
Re-RAC flowchart Abbreviations: RAC = residential aged care; Re-RAC = Reablement in RAC, TAU = treatment as usual * According to sample size calculation

The study will be conducted as a superiority trial, evaluating differences in treatment outcomes between the two groups, randomized in a 1:1 ratio. Additionally, an incremental cost–utility analysis will be performed to evaluate the cost-effectiveness of the intervention. Individual interviews analyzed using qualitative thematic analysis [29] will be conducted to explore the older adults’ experiences of the intervention, while analysis of focus-group interviews with staff will follow the methods described by Kreuger and Casey [30] and Dahlin-Ivanoff and Holmgren [31].

This protocol follows the Standard Protocol Items: Recommendations for Interventional Trials (SPIRIT) guidelines [32]. The study will be reported in several papers according to the Consolidated Standards of Reporting Trials (CONSORT) guidelines [33], the Consolidated Criteria for Reporting Qualitative Research (COREQ) [34], and the Consolidated Health Economic Evaluation Reporting Standards (CHEERS) [35].

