The present study aims to recruit 86 participants to detect a moderate-sized treatment effect. Clinical studies often encounter several challenges, including the quality of the outcome measures used, adherence to the intervention, and data collection [63]. In the planned PrRCT, these challenges may be amplified due to the frailty of the older adult participants. Data collection in such a population is inherently challenging, as seen in earlier studies [64, 65]. To address this, this study has limited the number of assessments and outcome measures and will conduct the assessments as structured interviews. This approach was tested in the feasibility study, which demonstrated that neither the participants nor the staff found the data collection process overly demanding [28]. However, it may be difficult to reach the estimated sample size in the included RAC facilities, so we have the municipality’s approval to include additional RAC facilities if needed. Furthermore, to gain a comprehensive understanding of the intervention’s impact on the older adults, nursing staff, and overall healthcare, the intervention will be evaluated using quantitative, qualitative, and health-economic methods. These diverse methods provide multiple perspectives, thereby enriching the findings.

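### With the printed inputs, 43 per group gives about 78% power at 25% dropout, not the stated 80%; the shortfall is small and restating the figure corrects it

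*Protocol article*

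**What the plan says.** All the inputs are in the protocol article under Sample size {14}. The target is given as "A total of 86 individuals (*n* = 43 per group) will be included to detect an improvement of 0.9 units in the primary outcome". The operating characteristics follow: "This calculation assumes 80% power", with "a significance level of *α* = 0.05, and a two-sided *t*-test". The variability and loss assumptions are "a standard deviation of 1.3 units for the change in COPM-P, and a 25% dropout rate". Trial design {8} gives equal allocation ("randomized in a 1:1 ratio").

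The same section then expresses the 0.9 units as a Cohen's d of 0.5 on a baseline standard deviation of 1.8 ("This corresponds to a moderate effect size"), and the Discussion repeats the label: "The present study aims to recruit 86 participants to detect a moderate-sized treatment effect".

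The section does not say how the dropout allowance was applied. The planned comparison, under Statistical methods {20a}, is not the t-test used for sizing. It is an analysis of covariance with baseline value and centre as covariates, and missing data are multiply imputed.

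**The concern.** Difference, standard deviation, test, significance level, power, dropout and group size are all printed, so they can be checked against each other. They do not agree. To have a required number of completers left after a fraction *d* drops out, that number is divided by 1 − *d*. Adding the same percentage to it gives too few, because the loss is then taken from the larger, inflated number.

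This is the only sample-size justification for the primary outcome. The article itself expects that frailty may affect retention (section {18b}) and that the target number may be hard to reach (Discussion). A research team that believes a 25% loss is covered at 80% power has somewhat less margin than it thinks.

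**Working it through.** **Inputs** (all from Sample size {14}): difference δ = 0.9; standard deviation of change σ = 1.3; two-sided α = 0.05; power 80%; two-sample t-test, 1:1; dropout 25%; 43 per group.

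**Step 1. Completers needed.** The standardised difference is δ/σ = 0.9/1.3 = 0.692. Solving the noncentral t power function for 80% gives *n* = 33.74, so 34 per group. Power at 34 is 80.3%.

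**Step 2. Reproducing the stated 43.**

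| Route | Per group | Total |
|---|---|---|
| t-test, add 25%: 34 × 1.25 = 42.5 | 43 | 86 |
| t-test, divide: 34/0.75 = 45.3 | 46 | 92 |
| t-test, divide before rounding: 33.74/0.75 = 44.99 | 45 | 90 |
| Normal approximation (33 completers), divide: 33/0.75 | 44 | 88 |
| Normal approximation, add 25%: 33 × 1.25 = 41.25 | 42 | 84 |

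Of these routes, only the first gives 43 and 86.

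**Step 3. What 43 per group delivers at 25% dropout.** Completers: 43 × 0.75 = 32.25 per group.

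| Completers per group | t-test power for 0.9 | Difference detectable at 80% |
|---|---|---|
| 32 | 77.8% | 0.925 |
| 32.25 | 78.1% | 0.921 |
| 34 | 80.3% | 0.896 |

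This result does not depend on which formula was used to reach 43.

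**Step 4. Dropout that 43 per group can absorb.** 1 − 34/43 = 0.209, so about 21%.

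**Step 5. The planned analysis of covariance.** Its power depends on the follow-up standard deviation, which the article does not give, so a range is assumed. With baseline standard deviation 1.8, change standard deviation 1.3 and follow-up standard deviation *s*, the implied correlation is *r* = (1.8² + *s*² − 1.3²)/(2 × 1.8 × *s*), and the residual standard deviation is *s*√(1 − *r*²).

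| Assumed *s* | *r* | Residual SD | Power, 32 per group |
|---|---|---|---|
| 1.6 | 0.71 | 1.12 | 89% |
| 1.8 | 0.74 | 1.21 | 83% |
| 2.0 | 0.77 | 1.27 | 79% |

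These figures ignore the few degrees of freedom spent on baseline and centre.

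**Step 6. The quoted d.** 0.9/1.8 = 0.50, as stated. On the change-score scale the same 0.9 units is 0.69 standard deviations (Step 1).

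**The case against.** **The inflation formula is not stated.** The printed 0.9 and 1.3 are one-decimal figures from a feasibility study that is not at hand. An unrounded standard deviation of 1.26 with difference 0.9, or a difference of 0.93 with standard deviation 1.3, needs 32 completers, and 32/0.75 = 42.7 gives 43 by correct division. So 43 alone does not prove that 25% was added. This stands: the mechanism is an inference, although the exact match at the printed values makes it the likeliest one. Rounding could equally run the other way (a standard deviation of 1.34 needs 36 completers), so it does not rescue the statement as printed.

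**The consequence is small.** About 2 points of power and 0.02 units on a 1–10 rating lie well within the uncertainty of feasibility-study inputs. The planned baseline-adjusted analysis is usually more efficient than the t-test and may bring power back above 80%. This also stands, and it limits the weight of the point. But the sample-size section rests on the t-test, and the recovery needs a follow-up standard deviation or correlation that the article does not give. Multiple imputation should not be counted on to replace the participants lost.

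**A stronger reading that does not hold.** A reader might infer from the d of 0.5 and the moderate label that the trial is powered for a different effect from the one claimed, and is badly underpowered for it. The documents do not support this. The baseline standard deviation is named beside the d, the division is exact, and the effect powered is the same 0.9 units on either scale. Results will also be reported as adjusted mean differences with 95% confidence intervals, so interpretation does not depend on d. At most, the Discussion repeats the label without its standardiser.

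**Conclusion.** The stated size, power and dropout do not hold together. On the printed inputs and the named t-test, 86 randomised with 25% dropout leaves about 32 per group and gives about 78% power (77.8% to 78.1%), with a detectable difference of about 0.92. The 80% claim is true only up to about 21% dropout. Against correct division, 86 is 6 short of 92, or 4 short of 90 if inflated before rounding.

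The calculation takes 0.9, 1.3 and 25% at face value. That 25% was added rather than divided out is likely but not documented. The error is in a headline figure but is minor in size, and it does not show that the trial is materially underpowered: under the planned analysis of covariance, power with 32 per group is about 79% to 89% for assumed follow-up standard deviations of 2.0 down to 1.6. The quoted d of 0.5 is not an error.

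**What to change.** Correct the statement in Sample size {14} and say how dropout was applied. Any one of these will do:

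- Keep 86 and state that 25% dropout leaves about 32 evaluable per group, with about 78% power for 0.9 units by t-test.
- Keep 86 and state 80% power with dropout of up to about 21%.
- Keep 86 and justify it by the planned baseline-adjusted analysis of covariance, giving the assumed follow-up standard deviation or baseline-to-follow-up correlation and its source.

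These change only the wording and need no extra participants. If 80% by t-test at 25% dropout is to be kept as stated, the target becomes 92 (90 if inflated before rounding), which means 4 to 6 more participants; the article already provides for adding facilities.

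Optional: give 0.69 on the change-score scale beside the d of 0.5, and name the baseline standard deviation where the Discussion uses the moderate label.
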